#### (ii) The explanatory questions

These will be examined using a mix of three mutually informative methods:

(a) For the MBCT arm time to relapse/recurrence of depression will be compared using Cox regression proportional hazard survival analysis, allowing for the stratification variables and any group differences in ADM tapering/usage (if rates of tapering/usage are different across the two arms).

(b) Mediational analyses will investigate hypothesised mechanisms of change pre-/post-treatment across the trial arms using approaches to testing mediation that allow multiple mediators in one model using the approach set out by Kraemer et al. (2002) and as used in our exploratory trial [49].

(c) Qualitative data will be analysed using thematic analysis (with NVivo software). This will combine inductive and deductive approaches and will be conducted collaboratively by a small sub-group of the research team in order to enhance validity.

The Data Monitoring and Safety Committee will oversee analysis at 3 and 12 months for patient safety and at 12 and 24 months for the primary outcome analyses. Given the public health importance of the findings we anticipate disseminating the findings at 12 and 24 month follow-ups as soon as they are available.

(d) Differences in mean costs will be analysed using standard parametric t-tests with the validity of results confirmed using bias-corrected, nonparametric bootstrapping (repeat re-sampling) [50]. Despite the skewed nature of cost data, this approach is recommended to enable inferences to be made about the arithmetic mean [51]. The primary economic analysis will focus on the policy question: MBCT vs. mADM. Cost-effectiveness will be assessed through the calculation of incremental cost-effectiveness ratios (ICER) and will be explored in terms of relapse/recurrence and quality adjusted life years using the EQ-5D measure of health-related quality of life. Uncertainty around the cost and effectiveness estimates will be represented by cost-effectiveness acceptability curves [52].

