#### Process data

Our explanatory question asks "is an increase in mindfulness skills the key mechanism of change of MBCT?" We address this via embedded quantitative and qualitative process-outcome studies across the trial arms. Quantitative measures will be administered at baseline and again one month after the end of the MBCT (or the equivalent time point in the m-ADM arm) so that change scores can be used to predict treatment outcome at the different follow ups using mediational analyses [28]. Critically, this design ensures that changes in putative mediators temporally precede the primary outcome (relapse/recurrence), a prerequisite in inferring mediation, and allows baseline-to-post-treatment change in symptoms to be statistically controlled. The same measures will be administered at study end to assess stability of change. We will also use experience sampling methods on sub-samples at study end to test emerging models of emotion regulation post-MBCT. All these assessments will comprise validated questionnaire and cognitive-experimental measures of the variables that we hypothesise mediate MBCT's effects.

In addition, qualitative data will be collected via semi-structured interviews and written responses to access patients' own accounts of the mechanisms and impacts of treatment. At the end of treatment (or the equivalent time point in the m-ADM arm), all participants will write short accounts of their experiences of and perceived impacts of treatment in response to open-ended questions. We will collect similar data from all participants at the end of the trial in order to gain a broad understanding of the impacts of both MBCT and ADM tapering and m-ADM over the follow-up period. Additionally at trial end, semi-structured interviews designed to obtain a more in-depth understand of the ongoing mechanisms and impact of treatment over the follow-up period will be conducted with sub-samples. Interviews will focus on the patients' views of the role of mindfulness, strategies to prevent or cope with relapses, and broader impacts of treatment in patients' lives, and will be informed by previous work on experiences of MBCT [26]. Integration with the quantitative process data will enhance understanding of change mechanisms that can improve MBCT's potential efficacy.

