### Statistical analysis plan

Analyses will be conducted by the trial statistician (RT) following CONSORT standards and overseen by the Data Monitoring and Safety Committee. Initial analyses will be conducted on an intention to treat (ITT) basis, with subsequent analyses being per protocol. All statistical models will be run with and without adjustment for baseline characteristics where the covariate selection is derived from comparison of the treatment groups at baseline.

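### Choosing baseline covariates by comparing the arms does not suit the mediation models: confounders of the mindfulness-to-relapse path are balanced between arms in expectation and are rarely selected

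*Protocol article*

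**What the plan says.** The opening paragraph of the Statistical analysis plan section sets a general rule: "All statistical models will be run with and without adjustment for baseline characteristics where the covariate selection is derived from comparison of the treatment groups". The comparison meant is the one made before treatment starts. The paragraph makes no exception for the mediation models.

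Under (ii) The explanatory questions, method (b) reads: "Mediational analyses will investigate hypothesised mechanisms of change pre-/post-treatment across the trial arms using approaches to testing mediation". The technique is given by citation and by reference to the exploratory trial. No baseline covariate is named.

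Method (a) in the same section is run "allowing for the stratification variables and any group differences in ADM tapering/usage", and the primary Cox model under (i) The policy question also allows for the stratification variables. Under Randomisation these are locality and symptomatic status, the latter split at a GRID-HAMD score of 8.

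The Process data section adds three provisions specific to mediation:
- Mediators are measured at baseline and one month after MBCT ends, so that "change scores can be used to predict treatment outcome at the different follow ups using mediational analyses".
- On timing, "this design ensures that changes in putative mediators temporally precede the primary outcome (relapse/recurrence), a prerequisite in inferring mediation".
- The design also "allows baseline-to-post-treatment change in symptoms to be statistically controlled".

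**The concern.** A mediation analysis has two links. Arm to mindfulness gain is a randomised comparison. Mindfulness gain to relapse is not: it compares patients who happened to gain more with patients who gained less, and a baseline characteristic that drives both gain and relapse distorts it. Intake severity and episode history are obvious candidates.

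The general rule looks for variables on which the arms differ. Whether the arms differ on a variable in a randomised trial is chance, and says nothing about whether it confounds the second link. Symptomatic status is also a stratification factor, so it is balanced by design and even less likely to be picked.

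At stake is the explanatory question, whether a gain in mindfulness skills is the key mechanism. Confounding of this path can suggest a mechanism that is absent or mask one that is present, depending on its sign.

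**Working it through.** The protocol gives no figure to reproduce here. The check asks how often the rule selects a confounder, and how much bias the other provisions leave. From the documents: 420 patients (taken as 210 per arm), hazard ratio 0.63, 20% attrition, and 60% relapse on m-ADM (the exploratory trial's 15-month figure, used as a 24-month assumption). All confounding strengths are assumptions.

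**1. The selection rule (linear illustration).** A baseline variable U affects mediator M and outcome Y with the same standardised coefficient c; M has no effect on Y; all variances are 1 within arm. The rule is read as a two-sided p < 0.05 comparison of arms.
- Expected spurious M-to-Y coefficient without U: c × c, which is 0.04, 0.09 and 0.16 for c = 0.2, 0.3 and 0.4. Simulation (4,000 trials each): 0.039, 0.090, 0.160.
- Chance that the rule selects U: about 5% whatever c is. Simulated: 5.0%, 5.5%, 5.0%.
- Expected coefficient under the rule: about 0.95 × c², which is 0.038, 0.086 and 0.152. Simulated: 0.037, 0.085, 0.152.
- With U always in the model: 0.00 in all three cases.

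So the rule leaves about 95% of the bias in place.

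**2. What symptom-change control removes.** Let X be intake severity and S post-treatment severity, both with SD 1 and correlation r. Change is S − X.
- Squared correlation of change with X: (1 − r)² / (2 − 2r) = (1 − r)/2.
- For r = 0.3 this is 0.35; for r = 0.6 it is 0.20.
- The share of X left uncontrolled is therefore 0.65 to 0.80, and about that share of the spurious coefficient remains: roughly two thirds to four fifths.

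Time ordering rules out relapse causing the mediator change. It does not act on a common baseline cause.

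**3. False-positive rate for the mindfulness-to-relapse path (Cox simulation).** Mindfulness has no effect on relapse, MBCT raises it by 0.5 SD, and severity correlates −0.2 or −0.3 with mindfulness gain. Severity carries a relapse log hazard ratio of 0.3 or 0.5 per SD (exp 0.3 = 1.35; exp 0.5 = 1.65). The rates below span these settings and several sets of runs of a few hundred trials per setting, so each is uncertain by a few percentage points.

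| Terms in the relapse model | Path significant at 5% |
|---|---|
| Arm, mindfulness gain | about 11% to 52% |
| Plus symptom change | about 9% to 35% |
| Plus symptom change and binary symptomatic status | about 5% to 12% |
| Arm, mindfulness gain, continuous intake severity | about 3% to 6% |

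The second row is nearest to what the article describes for method (b). The first omits the symptom-change control and should not be quoted as the plan's error rate.

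**4. Size on the effect scale.** With neither symptom change nor severity in the model, the spurious indirect effect is about 6% to 15% of ln(0.63) = −0.46. As a rough product: 0.5 × 0.2 × 0.3 = 0.03 and 0.5 × 0.3 × 0.5 = 0.075, set against 0.46. Symptom-change control reduces this by the share in step 2.

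**The case against.** The strongest reply is that the general rule adds covariates and does not forbid others. The article itself adds terms not chosen by arm comparison: the stratification variables in the primary model and method (a), and symptom change for mediation. On this view the problem in (b) is mostly silence. Its method is given by citation, and a covariate list is the kind of detail an article leaves to a fuller plan.

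Much of this stands. A reader might infer that comparing the arms is the plan's only covariate provision, or that the mediation models will have no other adjustment. The documents support neither. Nor do they say that the stratification variables are left out of (b), only that (b) does not mention them. If they are included, most of the excess error from this one confounder goes, as the third row of the table shows. The absence of a sensitivity analysis for unmeasured confounding is an omission that a fuller plan may fill, not an error. The bias is also modest on the effect scale, and (b) is one of several methods brought to the mechanism question.

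What does not fall is the rule itself. It is stated, it covers all models, and nothing shown exempts mediation. As the means of choosing baseline covariates for this path it has no connection with what confounds the path.

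**Conclusion.** The point holds in limited form. The stated way of choosing baseline covariates is unsuited to the mediation models, and the provisions in the Process data section narrow the gap without closing it. Under the assumed confounding, the false-positive rate for the path is roughly 9% to 35% with symptom-change control, against about 5% with intake severity included. The range depends on assumed correlations, hazard ratios and baseline-to-post symptom correlation, none of which the documents give; it shows direction and order of size, not a prediction. The policy question and the primary Cox comparison of the arms are unaffected. The change is worth making because an explanatory aim of the trial leans on this path and the remedy is nearly free.

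**What to change.** In (ii)(b), state that both the mediator model and the relapse model include, whatever the balance between arms, the continuous intake GRID-HAMD score, the baseline level of the mediator, and locality. Add the number of previous episodes if it is recorded: eligibility requires three or more, but the article does not say that a count is kept. State also that the general covariate rule does not govern these models. The symptom-change control can stay as already planned.

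Intake GRID-HAMD and locality are needed for randomisation and the mediators are measured at baseline, so no new data are required. The cost is a sentence or two and a few degrees of freedom. A sensitivity analysis for unmeasured confounding of the path would be a useful but optional addition.

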## Methods/Design

### Design

The design is a single blind, parallel RCT examining MBCT vs. m-ADM with an embedded process study. To answer the main policy research question: "Is MBCT superior to maintenance antidepressant medication (m-ADM) in preventing depression over 24 months?" the proposed trial compares MBCT plus ADM-tapering with m-ADM for patients with recurrent depression. Depressive relapse/recurrence over two years is the primary outcome variable.

The trial will answer the explanatory question "Is an increase in mindfulness skills the key mechanism of change?" in two mutually informative ways: quantitative measurement of potential mediating variables pre/post-treatment [28] and an embedded qualitative study to elicit service users' experiences of treatment.

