### Interventions

#### Maintenance antidepressants (m-ADM)

As part of the inclusion criteria, patients eligible to take part must be receiving treatment with antidepressant medication in line with the BNF and 2009 NICE guidelines. The m-ADM relapse/recurrence prevention intervention will be an extension of the ADM treatment that is an inclusion criterion for the study. In the UK almost all ADM prescriptions are issued by GPs [32]. Therefore GPs will be responsible for patients' ADM treatment in line with NICE guidelines and contemporary best practice [11]. NICE recommends that patients be maintained on ADM for 2 years after achieving remission, and then should only be tapered in accordance with the NICE guidance for recurrent depression. The guideline recommends that factors such as age, co-morbidity and other risk factors should inform the use of longer-term m-ADM. In the exploratory trial, at study entry the mean time on m-ADM was 340 days, with a significant distribution of patients who had been taking m-ADM for many years. The NICE guidance also speaks to monitoring, ADM type, dose, switching and augmentation.

Medication adherence will be monitored through patients' self-report using the Adult Service Use Schedule (AD-SUS) [33] and the Morisky Medication Adherence Instrument [34] and through manual checks of the GP practice databases at 12 and 24 month follow-ups. We will encourage patients to adhere to medication for the full length of the trial by writing to both the patient and their GP explaining that they have been randomised to maintenance antidepressants and asking them to continue to take a therapeutic level of antidepressants for the 2-year duration of the trial.

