### Sample size

Different relapse prevention interventions with different populations produce different absolute rates of depressive relapse/recurrence. Therefore, we have based our sample size on estimated hazard ratios for MBCT *vs*. m-ADM rather than estimated absolute relapse/recurrence rates. We canvassed service users and clinicians who concurred that a relative reduction in relapse/recurrence of 10% would be clinically important. ***(i) The policy question: ***The systematic review of MBCT *vs*. usual care for patients with recurrent depression reports hazard ratios of .47 and .28 for the key trials [24]. We applied several conservative assumptions (first row of Table 1). First, even though the exploratory trial data suggest that the hazard ratio was improving in favour of MBCT as the length of follow-up increased [25], we assumed the hazard ratio of .63 at 15 months to power the proposed trial at 24-months follow up. Second even though attrition from MBCT trials to date is consistently <15%, we have assumed an attrition rate of 20% over the 24-months of follow-up. Finally, we assumed there may be a small clustering effect (ICC = 0.01). The resultant sample size calculation assumptions and output are shown in Table 1 based on 80% power and significance set at .05. This leads to a total sample size of 420 across the two groups.

**Table 1 T1:** Sample size calculation

Author	Comparison	Mean hazard ratio	ICC	Design factor**	Attrition rate	**Sample size per group**^**a**^
Conservative scenario	MBCT *vs*. m-ADM	0.63	.01	1.11	20%	210

Kuyken et al., 2008 [25]	MBCT *vs*. m-ADM	0.63	-0.02	1.0	7%^a^	160

Ma & Teasdale, 2004 [22]	MBCT *vs*. usual care	0.28	-0.008	1.0	3%^b^	14^c^

Teasdale et al., 2000 [23]	MBCT *vs*. usual care	0.47	-0.04	1.0	5%^b^	41^c^

Sample size necessary for 90% power at 5% significance at 24 months;

^a ^at 15 months; ^b ^at 60 weeks, ^c^assuming exponential survival function.

Note group size of 12

***For the secondary outcomes***, meta-analyses of generic mindfulness approaches suggest medium effect sizes in changes in depressive symptoms [19,40] and our exploratory trial suggests medium effect sizes for the secondary outcomes of residual depressive symptoms, psychiatric co-morbidity and quality of life [25]. The sample size estimate for our policy question will enable us to detect a medium between-groups effect size (standardised mean difference or Cohen's d = 0.40) on the main secondary outcomes.

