#### Primary outcome

The occurrence of any depressive relapse/recurrence, and time from randomisation to relapse/recurrence, will be assessed using the Longitudinal Interval Follow-up Evaluation, a form of the Structured Clinical Interview for DSM-IV (SCID) [41,42] designed for longitudinal studies of depression. A patient will be judged to have had a relapse/recurrence if s/he was diagnosed as having a major depressive episode (a score of 5 for 2 consecutive weeks) at any time during the 24-month follow-up period.

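### The plan anticipates releasing 12-month primary outcome findings while some participants are still in the 24-month follow-up that defines the primary endpoint

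*Protocol article*

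**What the plan says.** All in the Protocol article:

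- **Question (Design):** "Is MBCT superior to maintenance antidepressant medication (m-ADM) in preventing depression over 24 months".
- **Endpoint (Primary outcome):** a major depressive episode "at any time during the 24-month follow-up period", with time to relapse measured from randomisation.
- **Sample size:** the text uses "80% power and significance set at .05", and the note under Table 1 places the calculation at 24 months.
- **Analyses (last paragraphs of the statistical analysis plan, under The explanatory questions):** the task set for the Data Monitoring and Safety Committee is to "oversee analysis at 3 and 12 months for patient safety and at 12 and 24 months for the primary outcome analyses".
- **Release (same paragraph):** "we anticipate disseminating the findings at 12 and 24 month follow-ups as soon as they are available". The reason given is the public health importance of the findings.
- **Blinding (Design):** the trial is described as single blind. Patients and GPs know the allocation: in the m-ADM arm both are written to, "asking them to continue to take a therapeutic level of antidepressants for the 2-year duration of the trial". In the MBCT arm patients are invited to taper with GP support, and the tapering section accepts that some patients or GPs will decide not to.
- **Entry (Setting, participants, recruitment and randomization):** participants are recruited in five time slices across four localities, so they reach 12 and 24 months on different dates. The length of recruitment is not given.

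**The concern.** The endpoint, the question and the sample size all refer to 24 months, but the dissemination sentence makes a between-arm comparison public about halfway through that window for the last recruits. The text puts no limit on who sees the 12-month comparison; it says only that the committee oversees the analysis.

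This design is open to influence from such a release. Whether a patient stays on ADM or tapers is part of the treatment contrast, and people who know the allocation decide it. A 12-month result in either direction could alter ADM use. It could also affect who stays in the study, and what participants report at an interview that relies on their own account. Later analysis cannot undo such an effect. The Background argues that trials reaching beyond one year are needed, and the second year is the part that early release puts at risk.

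A second question is whether two analyses labelled as primary, with one stated level of 0.05, raise the false-positive rate.

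**Working it through.** **1. The plan's own figure.** The stated 210 per group is consistent with one test at 0.05. The sample size section gives no relapse rate, so I assume 60% in the control arm (the exploratory trial's 15-month rate) and a two-sided test.
- MBCT relapse at HR 0.63: 1 − 0.40^0.63 = 43.9%.
- Two proportions, 80% power: 150 per group. With the design factor and attrition: 150 × 1.11 / 0.80 = 208.1, so about 209 against 210.

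The match does not identify the authors' method. The Table 1 note says 90% power where the text says 80%, and 90% power with relapse extrapolated to 24 months gives about 206. That conflict is a separate matter.

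**2. Relapse model.** I assume exponential relapse with 60% at 15 months in the control arm: λ = −ln(0.40)/15 = 0.0611 per month. The MBCT hazard is λ × HR, with HR 0.63 (Table 1) or 1.

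| | Relapse by 12 months | Relapse by 24 months |
|---|---|---|
| Control, and MBCT at HR 1 | 52.0% | 76.9% |
| MBCT at HR 0.63 | 37.0% | 60.3% |

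Share of 24-month relapses that occur by each participant's month 12:
- HR 0.63: (52.0 + 37.0)/(76.9 + 60.3) = 0.648.
- HR 1: 52.0/76.9 = 0.675.

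About one third therefore fall in the second year. With staggered entry, only second-year time after the release date is exposed.

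**3. Relapses after release.** I assume uniform entry and release when the last recruit reaches month 12, with no attrition. With 12-month recruitment, follow-up at release is then spread evenly over months 12 to 24. The mean relapse-free proportion per arm is [S(12) − S(24)]/(12 × hazard).
- Control: (0.4805 − 0.2308)/0.7330 = 0.3405. Still to relapse by month 24: 0.3405 − 0.2308 = 0.1097, or 23.0 of 210.
- MBCT, HR 0.63: (0.6301 − 0.3971)/0.4618 = 0.5047. Still to relapse: 0.5047 − 0.3971 = 0.1076, or 22.6 of 210.
- HR 0.63, both arms: 45.6 of 288.1 expected relapses = 15.8%. Relapse-free at release: 210 × (0.3405 + 0.5047) = 177.
- HR 1, both arms: 46.1 of 323.1 = 14.3%. Relapse-free at release: 143.

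With 24-month recruitment, half the participants have completed 24 months at release, so these figures halve.

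| Recruitment length (assumed) | Share of relapses after release | In follow-up and relapse-free, of 420 | Share with an assumed 6-month lag |
|---|---|---|---|
| 12 months | 14–16% | about 140–180 | about 3–4% |
| 24 months | 7–8% | about 70–90 | about 2% |

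**4. Type I error.** The 12-month events are contained in the 24-month analysis, so the two Z statistics have correlation √t, where t is the information fraction at 12 months. With each test at two-sided 0.05, the chance that at least one is falsely significant is:
- 7.8% at t = 0.65;
- 7.6% at t = 0.70.

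These figures apply only if significance at either time counts as success. If 24 months alone is confirmatory and nothing stops at 12 months, the level is 0.05.

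**The case against.** **Multiplicity.** A reader might infer that the trial has two chances at significance and an error rate near 8%. The text does not support that. Question, endpoint and sample size all point to 24 months, and nothing says that a significant 12-month result would count as success or stop the trial. Any alpha rule or boundary may sit in an analysis plan or committee charter that is not shown. This objection stands. What remains is that the article calls both analyses primary outcome analyses and never says which one is confirmatory.

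**Size.** A reader might also take the whole second year, about one third of relapses, as exposed, or all 420 participants as open to influence. Staggered entry rules out the first. The second fails because a participant who has already relapsed can no longer change a time-to-first-relapse analysis. This objection stands too, and the smaller figures above follow from it.

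**Mechanism.** Patients and GPs know the allocation already, and the exploratory result favouring MBCT (47% against 60%) was already available. MBCT patients are encouraged to stop ADM within six months of their group's end, so much of that tapering would precede release. Aggregate results do not tell assessors an individual's arm, and the economic evaluation takes therapist contacts from therapist records to protect their blinding. These points weaken the case for assessor bias and leave the size and direction of any effect unknown. They do not remove the risk to continued ADM use, retention and self-report among participants still relapse-free.

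**Wording.** The sentence states an expectation and does not define findings. Even so, it follows directly on the 12- and 24-month primary outcome analyses, and nothing in the text withholds the arm comparison.

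**Conclusion.** The concern holds as a risk to the 24-month comparison, and it should be fixed. The plan as written allows arm-level results on the primary outcome to become public while part of the primary follow-up is unfinished.

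On the assumptions in the working, about 14–16% of 24-month relapses would follow release with 12-month recruitment and about 7–8% with 24-month recruitment. Any publication lag lowers these shares. They measure how much of the endpoint is exposed; the documents give no basis for estimating how large a bias would result. The recruitment length, entry pattern, relapse curve and release date are all assumptions.

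An inflated type I error is not established. It would be about 7.6–7.8% only under a rule that either analysis can establish superiority, and the article contains no such rule.

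**What to change.** Change the paragraph on the Data Monitoring and Safety Committee in three ways:

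1. Name the Cox analysis of time to relapse/recurrence over 24 months as the only confirmatory test of the primary outcome, at the stated 0.05 level.
2. Say that 12-month comparative results are confidential to the Data Monitoring and Safety Committee.
3. Replace the dissemination sentence with wording such as: No outcome results by trial arm will be released until the last participant has completed 24 months of follow-up; 12-month and 24-month findings will then be reported together.

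The sample size of 420 is unaffected. The cost is one paragraph of text and a delay of up to about a year in publishing the 12-month findings. The change has to be made before the 12-month analysis, because disclosure cannot be reversed.

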***Randomisation ***will use permuted block randomisation using computer generated quasi-random numbers. Randomisation will be stratified according to recruitment locality (4 sites, enabling a steady flow to treatment groups) and participants' symptomatic status at intake assessment (asymptomatic *vs*. partially symptomatic), using the GRID-Hamilton Rating Scale for Depression GRID-HAMD [31] cut-off of less than eight being asymptomatic and greater than or equal to 8 being partially symptomatic.

Figure 1 summarises the trial Consort diagram.

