#### (i) The policy question

For the primary outcome variable, time to relapse/recurrence will be compared using Cox regression proportional hazard survival analysis with treatment condition (MBCT/m-ADM) as the independent variable and allowing for the stratification variables. In a secondary analysis ADM use will be added as an independent variable in the Cox regression model. A per protocol analysis will also be undertaken for the secondary outcomes.

Secondary outcomes will be examined using mixed models Analysis of Variance (ANOVA): between group (ITT/per protocol) and repeated measures (3-24 month follow-ups). Sensitivity analyses will explore the impact of imputation of data losses including loss to follow up and drop out.

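### The cost comparison is fixed as a two-sample t-test that leaves out the randomisation strata, so its standard error is somewhat too large; adding the strata costs nothing

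*Protocol article*

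**What the plan says.** All references are to the protocol article.

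- **Cost analysis** (Statistical analysis plan, (ii) The explanatory questions, item (d)): "Differences in mean costs will be analysed using standard parametric t-tests". A bias-corrected bootstrap is to confirm the result, and the stated reason is inference on the arithmetic mean despite skewed costs. No covariate or stratum is named.
- **Allocation** (Setting, participants, recruitment and randomization): "Randomisation will be stratified according to recruitment locality", with four sites, and also by "participants' symptomatic status at intake assessment", split at a GRID-HAMD score of 8. Permuted blocks are used.
- **Primary analysis** ((i) The policy question): Cox regression with treatment condition "as the independent variable and allowing for the stratification variables".
- **General rule** (Statistical analysis plan, opening paragraph): "All statistical models will be run with and without adjustment for baseline characteristics", where "covariate selection is derived from comparison of the treatment groups at baseline".
- **Effect side of the ICER** (item (d)): cost-effectiveness is "explored in terms of relapse/recurrence and quality adjusted life years using the EQ-5D measure". No model for the QALY contrast is given.

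**The concern.** The trial randomises within strata and analyses its primary outcome accordingly, but names a cost method that cannot do the same. This is a stated choice of method, not a detail left to a fuller document.

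Stratified allocation removes the between-stratum part of the variance from the true sampling error of the cost difference. The t-test standard error still includes that part, so the interval is too wide wherever locality or symptom status predicts service use. Resampling patients within arm addresses skewness but reproduces the same unadjusted variance.

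Cost-effectiveness is a listed secondary outcome of the policy question. The spread of the acceptability curve depends directly on the precision of the cost difference, so at stake is avoidable imprecision in that result.

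**Working it through.** The article states no precision or power for the cost contrast, so there is no figure of its own to reproduce.

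**Does the general rule already cover the point?** Set beside item (d):

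1. The rule speaks of statistical models run in two versions. A two-sample t-test has only an unadjusted version. Either the rule does not reach costs, or item (d) is incomplete.
2. The rule selects covariates by how the arms compare at baseline. Permuted blocks within the 4 × 2 = 8 locality-by-symptom cells hold these factors close to balance, so a rule driven by observed difference would seldom select them. Their claim to inclusion is that they define the allocation and may be prognostic.
3. Running models both ways does not say which cost estimate feeds the ICER.

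**How large is the loss?**

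Inputs from the article (Sample size): 210 per arm and 20% attrition, giving 210 × 0.80 = 168 analysed per arm. Assumed, because the article gives nothing: the strata explain a share R² of 1% to 15% of cost variance; alpha is two-sided 5%; the reference effect is the one detected with 80% power when R² = 0, namely (1.960 + 0.842) × √(2/168) = 0.306 SD.

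Formulas, with Φ the normal distribution function, for allocation balanced within strata:

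- overstatement of the standard error: 1/√(1 − R²)
- true size of the unadjusted test: 2 × [1 − Φ(1.960/√(1 − R²))]
- power, unadjusted: Φ(0.842/√(1 − R²))
- power, adjusted: Φ(2.802/√(1 − R²) − 1.960)

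| Assumed strata R² | SE overstated by | True size at nominal 5% | Power, t-test | Power, adjusted |
|---|---|---|---|---|
| 1% | 0.5% | 4.9% | 80.1% | 80.4% |
| 5% | 2.6% | 4.4% | 80.6% | 82.0% |
| 10% | 5.4% | 3.9% | 81.3% | 84.0% |
| 15% | 8.5% | 3.3% | 81.9% | 86.0% |

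The power given up runs from 0.3 to 4.1 points.

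**If baseline service-use cost is also collected.** The article does not say that it is. With a correlation r between baseline and follow-up cost (assumed), the adjusted variance is 1 − r² times the unadjusted one:

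- r = 0.3: the unadjusted SE is 1/√0.91 = 1.05 times the adjusted one, equivalent to needing 1/0.91 = 1.10 times the patients.
- r = 0.5: the ratios are 1/√0.75 = 1.15 and 1/0.75 = 1.33.

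**The case against.** The best reply is that the plan already promises adjusted and unadjusted runs, and that a t-test backed by a bootstrap is a reasoned choice for inference on mean cost. The error is also on the safe side: the test is conservative, and the unadjusted difference is unbiased over randomisations. Most of this stands. It rules out calling the analysis invalid and keeps the point small. It does not dispose of the point: as shown above, the general rule neither fits the named method nor would be likely to bring in the strata, and a linear regression keeps the arithmetic-mean scale that the authors want.

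A reader might go further and infer that the QALY contrast is unadjusted too, so that a chance gap in baseline utility passes into the ICER at a sizeable monetary value. The article does not support that. The t-test sentence concerns costs only, no QALY model is given, and no visit schedule places the EQ-5D at baseline. Such detail is commonly left to a fuller plan, and the Economic evaluation section defers to the exploratory trial's methods, which are not shown here. Any monetary figure would rest on assumed utility SDs, an assumed persistence of the gap over two years and an assumed threshold, so none is offered.

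Nor does omitting the strata carry material imbalance into the cost difference: blocking already keeps those factors close to balance.

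**Conclusion.** The point holds for costs, as a modest loss of precision. The named test ignores the factors the trial randomises by, although the primary analysis respects them, and the general adjustment rule does not close the gap. The consequence is a conservative test and an interval up to about 8.5% too wide at the top of the assumed R² range, and almost no loss at the bottom. There is no bias. These sizes assume stratum effects common to both arms, near-balance within strata and approximately normal sample means; the R² range is an assumption, not a figure from the article. The change is worth making because it costs almost nothing, not because the loss is large.

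**What to change.** In item (d), replace the t-test as the main cost analysis with a linear regression of cost on arm, locality and symptom status. Add baseline service-use cost as a prespecified covariate if the AD-SUS is given at baseline. Keep the arithmetic-mean scale and take bias-corrected bootstrap intervals for the adjusted difference. State that this estimate is the one used for the ICER and the acceptability curve; the t-test can remain as a supporting result.

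In the opening paragraph of the Statistical analysis plan, say how the general adjustment rule applies to costs, and that the stratification factors enter regardless of observed baseline differences. If the EQ-5D is measured at baseline, include that value in the QALY regression.

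The cost is a few lines of wording and negligible analysis time. The strata are known for every randomised patient, and the two further covariates are asked for only where already collected, so no new data are needed.
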